## Methods/Design

The study was approved by a Research Ethics Committee established by the NHS Health Research Authority (NRES Committee South West – Frenchay, REC reference 12/SW/0162 of 25 June 2012). This is a 6-month, prospective, observational study based on a convenience sample. We will recruit index participants from the pool of women referred to specialized domestic violence agency SURVIVE South Gloucestershire and Bristol for community outreach support or refuge accommodation by other agencies or self-referred. The SURVIVE agency is a charitable organization which provides a range of services to women who have experienced DVA, including three refuges for women with children, outreach support, community-based Freedom Program groups, Independent Domestic Violence Advisers, support phone line, and Information Sessions in South Gloucestershire, and Bristol UK.

Inclusion criteria for participants contain age ≥ 18 y.o. Exclusion criteria include inability to read English, current use of steroid-based medications, pregnancy, presence of pituitary and/or adrenal gland disorder, and symptomatic psychotic illness. No participant will be excluded on the basis of their disability, ethnicity, religion or sexual orientation.

### Recruitment

Potential index participants will be identified by written invitation letters with invitation slip attached offered by researcher or agency staff to every woman referred or self-referred to domestic violence agency SURVIVE. Woman willing to be approached to discuss potential participation in the study can either send her contact details to the researcher by phone or e-mail, or put down her contact details on the invitation slip, tear it off and return to the researcher or agency staff who has given the invitation to her.

The researcher will collect contact details sent by phone, e-mail, and completed invitation slips and phone all women willing to be approach to hear more about the study. When initial telephone contact has been made with a woman, the researcher will assess her eligibility and arrange a face-to-face meeting with all women interested and eligible to take part, meeting the woman at a safe and convenient place. As part of the first face-to-face meeting, the researcher will give a detailed participant information sheet to the woman, explaining each point and answer any questions that the woman may have prior to seeking her written informed consent.

The researcher will ask every woman already consented to participate in the study to suggest up to three female friends or family members of the same age group who are aware of her current circumstances to be her potential controls. The researcher will emphasize that suggesting friend controls is completely optional. If a woman does not want to recommend friend controls it will not affect her participation in the study nor the services she receives. If a woman wishes to suggest friends as potential controls the researcher will ask her to pass ‘An invitation to the CEASE study’ to those people. ‘An invitation to the CEASE study’ and all documentation for friend controls present the study as biological research on the impact of family stress on women's health and wellbeing and do not mention SURVIVE agency. Although it does state that the research is about DVA, the researcher will ask the index participant only to pass the invitation to confidantes who know that she has experienced abuse. A friend control willing to discuss potential participation in the study will send her contact details to the researcher by post, phone, text, or e-mail. The researcher will contact potential friend controls by phone to give brief information about the study, assess their eligibility and arrange a face-to-face meeting at a safe and convenient place. As part of the first face-to-face meeting, the researcher will give a detailed participant information sheet to the friend control, explaining each point and answer any questions that the woman may have prior to seeking her written informed consent. In parallel with recruitment of friend controls through index research participants we will approach potential controls in local communities through invitation letters displayed in public places (e.g. post office, library, supermarket, community centre) in areas surrounding SURVIVE sites in South Gloucestershire and Bristol.

### Measurements

This study will consist of one baseline and two follow-up measurements. Baseline evaluation will be carried out at the first face-to-face meeting between researcher and woman and during the following week. Women will be asked to undertake follow-up assessment at 3 and 6 months after joining the study. With regard to safety preferences participants will have a choice to receive and return follow-up questionnaire and saliva collection kit by post or at the follow-up face-to-face meeting with the researcher. Each assessment will last approximately 45 minutes and will include: (1) numerous standardized self-administered questionnaires to assess socio-demographics, mental and physical health, (2) weight and height measurement, and (3) self-completion of three saliva samples. The questionnaire and saliva samples will be completed by the participant at a place that is safe and convenient to her and returned by post or via collection by the researcher. Research plan and measurements are summarized in Additional file 2.

Socio-demographic information will be collected through use of a standardized self-report questionnaire and include age, ethnicity, children, qualifications, employment status, total annual income and relationship to perpetrator.

Exposure to abuse through the lifespan will be measured using two psychological instruments. First, cases of childhood abuse and neglect will be detected using the Childhood Trauma Questionnaire (CTQ). CTQ is a 28-item inventory that provides brief, reliable and valid screening for histories of abuse and neglect. The CTQ inquires about five types of maltreatment – emotional, physical, and sexual abuse, and emotional and physical neglect – with five items representing each type. Participants respond to a series of statements about childhood events, which are endorsed on a 5-point frequency scale (0 = “never true”, 4 = “very often true”). Item scores are then summed to produce scores that quantify the severity of maltreatment in each area and that can be compared to clinical data. Cut-off scores for detecting likely cases of abuse and neglect are also provided. The CTQ was validated with data from over 2,000 respondents, including both clinical and non referred groups [33]. Second, exposure to DVA from intimate partner and other family members will be measured using the Composite Abuse Scale (CAS). The CAS is a widely used self-report of behaviors that women describe as abusive by their partners [34]. It is an easily administered measure that provides standardized sub scale scores on four dimensions of DVA. It consists of 30 items presented in a six point format requiring respondents to answer “never”, “only once”, “several times”, “monthly”, “weekly” or “daily” in a twelve month period. The Severe Combined Abuse sub scale has 8 items that represent severe physical abuse items, all sexual abuse items, and physical isolation aspects of emotional abuse. The Emotional Abuse subscale has 11 items that include verbal, psychological, dominance and social isolation abuse items. The Physical Abuse subscale has 7 of the less severe physical abuse items and the Harassment subscale has 4 items that are about actual harassment. CAS is scored by summating the frequency scores of the 30 items. The 0–5 for each item thus gives a possible score for each sub scale. Cut-off scores to exclude women labeled abused incorrectly are provided. The CAS can give not only prevalence figures, but also associations with other physical and emotional co-morbidities. It has been used in specialized domestic violence agencies, general practice, antenatal clinics, emergency departments, and drug and alcohol clinics. The CAS has demonstrated good acceptability and reliability, with some evidence of criterion and external validity. To measure DVA duration an item is added to the CAS asking participants the length (“one occasion”, “up to 6 months”, “up to 1 year”, “up to 3 years”, “up to 5 years”, and “more than 5 years”) of abusive relationship.

Levels of stress and mental health of the participants will be evaluated using five psychological instruments for detecting the most common mental disorders alongside with standardized questionnaire on use of alcohol and drugs. First, the Generalized Anxiety Disorder Scale (GAD-7) will be used to screen on probable cases of generalized anxiety disorder and to assess symptom severity. The GAD-7 is based on the most prominent diagnostic features of the DSM-IV diagnostic criteria for generalized anxiety disorder and has excellent reliability, as well as criterion, construct, factorial, and procedural validity. The 7 items assess the frequency of core symptoms of generalized anxiety disorder within the past two weeks. Items are rated on a 4-point frequency scale (0 = “not at all”, 3 = “nearly every day”) with a total score ranging from 0 to 21. A score up to 4 indicates the absence of generalized anxiety disorder, scores of 5–9 represent mild, scores of 10–14 represent moderate and scores of 15 and higher represent severe anxiety symptoms levels [35].

Second, Patient Health Questionnaire Depression Scale (PHQ-9) will be used to diagnose major depression and assess symptom severity. The PHQ-9 is based on the DSM-IV diagnostic criteria for major depressive disorder and has excellent reliability, as well as criterion, construct, factorial and procedural validity. The 9 items assess the frequency of depressive symptoms within the past two weeks. Items are scored on a 4-point frequency scale from 0 = “not at all” to 3 – “nearly every day” with a total score ranging from 0 to 27. A cut-off point of >9 is recommended for the screening of any depressive disorder. A score up to 4 indicates the absence of depression, scores of 5–9 represent mild, scores of 10–14 represent moderate and scores of 15 and higher represent severe depression [35,36].

Third, PTSD will be diagnosed using the PTSD Symptom Scale: Self-Reported version (PSS-SR). The PSS-SR is a 17-item measure that assesses the 17 DSM-IV symptoms of PTSD. The severity over the last two weeks of each item on the PSS-SR is rated using a 4-point scale (0 = “not at all”, 4 = “every day”). The total score is calculated as the sum of severity ratings for the 17 items. The total score > 13 indicates on likelihood of PTSD. The PSS-SR has satisfactory internal consistency, high test-retest reliability, and good concurrent validity [37].

Fourth, the Sheehan Disability Scale (SDS) will be used to assess functional impairment in three inter-related domains; work/school, social and family life. The participant rates the extent to which work/school, social life and home life or family responsibilities are impaired by her symptoms on a 10-point visual analog scale. Score 5 or greater on any of the three scales is associated with significant functional impairment. The SDS has high sensitivity and good specificity for patients with most frequent mental disorders [38].

Fifth, the Perceived Stress Scale (PSS) will be used for measuring the perception of stress [39]. This widely used 10-item psychological instrument with good internal reliability and moderate construct validity measures the degree to which situations in one’s life are appraised as stressful over the past month. It assesses the amount of stress in one’s life rather than response to a specific stress and had been used in studies of both mental and physical health. The questions in the PSS ask about feelings and thoughts during the last month. In each case, respondents are asked how often they felt a certain way. Answers are rated on a 5-point frequency scale (0 = “never”, 4 = “very often”). PSS scores are obtained by reversing responses to the four positively stated items and then summing across all scale items. Scores can range from 0 to 40, with higher scores indicating greater stress.

Finally, use of alcohol and drugs will be measured by asking questions about quantity and frequency of substance use.

Physical health of the participants will be evaluated by body mass index (BMI) and a standardized questionnaire. To calculate BMI the researcher will follow standard clinical protocol on taking standing height and weight. Height will be measured to the nearest 1 mm (KaWe person-check, Germany), weight to the nearest 0.1 kg (Seca 803 Digital Personal Scale, Germany). Physical health problems will be measured using a modification of the Miller Abuse Physical Symptom and Injury Scale (MAPSAIS). This self-reported scale lists 9 injuries and 44 symptoms and illnesses related to DVA and asks if the woman was hospitalized, visited emergency department or undertaken surgery in the past 12 months. The scale was designed specifically for measuring long-term health consequences of DVA and demonstrated good content validity and test-retest reliability [40].

Upon completion of questionnaire and anthropometry study participants will be given a saliva sample collection kit that includes a saliva collection device (Salivette tubes) with cotton pledget, an illustrated instruction sheet written in plain language explaining the procedure and providing helpful hints (such as putting the tube next to the bed for morning sample), a saliva collection diary in which participants can record experiences on the day of sample collection and a prepaid packaging addressed to the accredited laboratory compliant with current postal regulations. The participants will be asked to collect three saliva samples as soon as possible after questionnaire survey:

1. Sample 1 “bedtime” – right before getting into bed.

2. Sample 2 “awakening” – next morning as soon as the woman wakes up and is ready to get up for the day.

3. Sample 3 “post-awakening” – 30 minutes after taking awakening sample.

Saliva will be collected by either passive drooling into the tube or by chewing (for 2 minutes) the cotton pledget provided with each tube. Participants must have waited at least 30 minutes after smoking, consuming any food or drink or teeth brushing before collecting the saliva sample. Tubes will be labeled with patient identifier and returned to the laboratory by post or via collection by the researcher. Upon arrival to the laboratory tubes with saliva will be centrifuged to remove the upper saliva layer for subsequent measurement of cortisol. The primary tube including the cotton pledget with individual cells will be then discarded in routine clinical waste. The upper saliva layer will be frozen until analysis. The saliva samples will be analyzed in the Department of Clinical Biochemistry at the Bristol Royal Infirmary using Ultra performance liquid chromatography – tandem mass spectrometry (UPLC-MSMS). The analysis also simultaneously measures cortisone a metabolite of cortisol as an additional measure of circulating cortisol [41,42].

To collect data on known covariates that have been related to diurnal cortisol secretion participants will complete saliva collection diary [22]. Data collected on the day of saliva sampling include: schedule (whether weekend vs. weekday), time of awakening, lifestyle (smoking, alcohol use, caffeine, exercise/activity level, perceived stress and negative mood, recent meal, medications) and menstrual timing.

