**Methods/Design:**

To meet study objectives 128 women will be recruited in a domestic violence agency and local communities. Baseline and 3-month follow-up measures will be taken over 6 months after recruitment. Each assessment will include: (1) standardized self-administered questionnaires to evaluate socio-demographics, experience of violence and abuse, mental and physical health; (2) weight and height measurement; (3) self-completion of wakening, post-wakening and evening saliva samples. Saliva will be analysed for cortisol and cortisone using Ultra performance liquid chromatography – tandem mass spectrometry.

We will compare diurnal cortisol parameters between non-abused controls and abuse survivors with and without mental health conditions. First following descriptive statistics for all the cortisol and mental health outcomes, relationships between them will be investigated using appropriate regression models. Second, these techniques will be used to investigate the extent to which cortisol measures act as potential mediators between type, severity, duration of abuse and mental disorders.

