### Statistical analysis

For the sample size calculation we used findings from similar studies in comparable populations [24,43,44]. Thus, the number of participants required to detect a standardized difference in cortisol levels of 0.5 between abused women and non-abused controls with 80% power using a cut-off score for statistical significance of 0.05 is 128 (64 per group). Assuming 40% drop out rate before the study ends, around 213 eligible subjects would have to be approached. Assuming 60% response rate we will have to approach approximately 355 women, so 213 would consent to join the study, and of these 128 would be expected to complete the study.

Data will be coded and entered into research database during data collection by the two researchers responsible for recruitment. Stata software will be used for statistical analysis. All data will be checked for expected ranges, presence of outliers and abnormal values.

Sample will be analyzed by comparison of participant exposed to DVA and participants without DVA exposure on the basis of cortisol and mental health state data. Primary study outcome will be reported as diurnal cortisol variation, the degree of decline in cortisol across the day. Secondary study outcomes include CAR, size of post-awakening surge in cortisol that occurs in 30 minutes after awakening and mean salivary cortisol concentration across the day. As an additional measure of tissue cortisol the three saliva samples, awakening, post awakening, and bedtime, will also be assayed for cortisone.

Following descriptive statistics for all the cortisol and mental health outcomes, relationship between them will be investigated using appropriate linear (and, for binary outcomes, logistic) regression models. Using the CAS and CTQ data, these techniques will also be used to investigate the extent to which cortisol measures act as potential mediator between the type, duration and cessation of abuse and mental health condition for this group of women.

Missing data from women who dropped out of the study will be handled first by comparing their baseline variables with those who completed the study, and secondly using imputation techniques [45].

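### Bedtime saliva is taken before the two morning samples, so the primary outcome (decline across the day) always joins two calendar days, and the bedtime value will often follow the abuse questionnaires

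*Protocol article*

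**What the plan says.** The Measurements section of the protocol article sets the order of events at an assessment.

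- **Kit hand-over:** "Upon completion of questionnaire and anthropometry study participants will be given a saliva sample collection kit".
- **Start of sampling:** "The participants will be asked to collect three saliva samples as soon as possible after questionnaire survey".
- **Sample 1 (bedtime):** "right before getting into bed".
- **Sample 2 (awakening):** "next morning as soon as the woman wakes up and is ready to get up for the day".
- **Sample 3 (post-awakening):** "30 minutes after taking awakening sample".

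No sample follows on the second evening, and none precedes the bedtime sample on its own morning.

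The Statistical analysis section defines the endpoint: "Primary study outcome will be reported as diurnal cortisol variation, the degree of decline in cortisol across the day". The secondary outcomes are the awakening response and the mean concentration across the day. The Discussion presents the three-point scheme, repeated at three waves, as providing the diurnal slope, and counts this as a strength.

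According to the abstract, each assessment includes "standardized self-administered questionnaires to evaluate socio-demographics, experience of violence and abuse, mental and physical health". The saliva diary collects its covariates, including weekday or weekend and time of awakening, for the day of sampling, in the singular.

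**The concern.** A decline across the day runs from a morning to the evening of the same day. The schedule instead yields an evening and the following morning, so it measures an overnight rise. To report it as a decline, the analyst must subtract the evening of day 1 from the morning of day 2. Two things are at stake.

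1. **Meaning and precision of the primary outcome.** The two ends of the slope belong to different days. If a woman's morning and evening values are more alike within a day than across two days, the difference is noisier than a same-day slope. A diary for a single day also cannot describe both days when, say, a Sunday bedtime is followed by a Monday waking.

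2. **A possible group-related artefact.** With bedtime first and a request to start promptly, the bedtime sample will often be taken a few hours after a woman has answered questions on abuse and PTSD symptoms. The Background section says that cortisol rises with acute stress. If recall is more stressful for survivors than for controls, bedtime cortisol would be raised more in survivors. Their slope would look flatter, which is one form of the altered diurnal rhythm that the study hypothesises.

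**Working it through.** **Step 1. The plan's own figure.** Inputs (Statistical analysis): standardized difference 0.5, 80% power, significance level 0.05. A two-sided two-sample t-test needs 63.8, so 64 per group and 128 in total; power at 64 per group is 80.1%. Allowing for drop-out, 128/(1 − 0.4) = 213.3; allowing for response, 213/0.6 = 355. The stated sample size reproduces and is not in question.

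**Step 2. Which samples share a day.**

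| Outcome | Samples used | Days |
|---|---|---|
| Diurnal variation (primary) | awakening, bedtime | day 2 and day 1 |
| Mean across the day | all three | days 1 and 2 |
| Awakening response | awakening, +30 min | day 2 only |

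This follows from the sampling order alone and holds at each of the three waves.

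**Step 3. Effect on power, under assumptions.** The protocol gives no correlations and no SDs. Take the slope as awakening minus bedtime, with waking SD 1, bedtime SD k, and correlation ρ. Then Var = 1 + k² − 2ρk. Let R be the across-day variance divided by the within-day variance. If 0.5 SD is the same-day effect, the effect actually seen is 0.5/√R and the equivalent group size is 64/R.

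| ρ within / across | k | R | Effect (SD) | Power, 64 per group |
|---|---|---|---|---|
| 0.3 / 0.3 | any | 1.000 | 0.500 | 80% |
| 0.3 / 0.25 | 1 | 1.50/1.40 = 1.071 | 0.483 | 77% |
| 0.3 / 0.25 | 0.3 | 0.94/0.91 = 1.033 | 0.492 | 79% |
| 0.2 / 0.1 | 1 | 1.80/1.60 = 1.125 | 0.471 | 75% |
| 0.3 / 0.15 | 0.3 | 1.00/0.91 = 1.099 | 0.477 | 76% |
| 0.3 / 0.15 | 0.5 | 1.10/0.95 = 1.158 | 0.465 | 74% |
| 0.3 / 0.15 | 1 | 1.70/1.40 = 1.214 | 0.454 | 72% |
| 0.4 / 0.2 | 1 | 1.60/1.20 = 1.333 | 0.433 | 68% |

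In the 0.3/0.15 case with equal SDs, 64 per group acts like 64/1.214 = 52.7. Where a loss arises, these scenarios span 68–79%. A wider gap lowers power further: 0.5 within, 0 across and equal SDs give R = 2, an effect of 0.354 SD and 51% power. That corner is extreme and nothing in the protocol points to it.

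**Step 4. Effect of a questionnaire reaction, under assumptions.** Suppose the reaction shifts the slope by b SD in survivors only. The noncentrality of the t-test is b√(64/2) = 5.657b. With no true difference, the chance of a significant result at a nominal 5% is:

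- b = 0.1: noncentrality 0.566, 9%
- b = 0.2: noncentrality 1.131, 20%
- b = 0.3: noncentrality 1.697, 39%

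If the shift instead opposed a true 0.5 SD difference, the net effects of 0.4, 0.3 and 0.2 SD would have power of 61%, 39% and 20%. The protocol supplies no value of b.

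**The case against.** The strongest case for the plan concedes the sampling order and disputes what is built on it. Most of these points stand.

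- **Power.** A reader might infer that the study really has about 72% power. The protocol does not support that. The loss appears only if the across-day correlation is assumed lower than the within-day one, and it shrinks if bedtime values vary less than waking values. The 0.5 is stated for cortisol levels, not for a same-day slope, and the calculation uses one wave where three are planned.
- **Questionnaire reaction.** A reader might infer that the primary result will be biased, that analysis cannot remove the bias, or that a positive result could not be interpreted. That goes too far. Nothing in the protocol shows that these instruments raise cortisol until bedtime. Baseline may extend over the following week and follow-up kits may be posted, so same-evening sampling is favoured, not fixed. Abuse instruments are absent from the Measurements section's own list for each assessment, though the abstract includes them. The diary records perceived stress and negative mood, each sample is assayed separately, so a difference driven by bedtime values would be visible as such, and the awakening response does not use the bedtime sample.
- **Sample clock times.** A reader might infer that these go unrecorded. The diary items are introduced as a list of inclusions in a condensed article, and the diary itself is not shown. This is not a finding.
- **Abstract.** It mentions "self-completion of wakening, post-wakening and evening saliva samples", which might be read as a contradictory order. It lists types of sample, not a sequence.
- **Cost.** Sampling over a full waking day is somewhat more demanding in a cohort with 40% assumed drop-out and real safety constraints.

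None of this puts a morning and an evening sample on the same day, and the article gives no reason for the order.

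**Conclusion.** The point holds as a mismatch between the sampling order and the primary outcome. As written, the decline across the day is not observed within one day at any wave. The mean across the day shares the defect; the awakening response does not. This follows from the text and needs no assumption.

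The consequences are conditional. Power may be unaffected, or may fall to roughly 68–79% in the main scenarios, depending on quantities the protocol does not give. The questionnaire reaction is a plausible group-related risk, not a demonstrated bias. It merits attention because even a 0.2 SD shift in survivors alone would take the false-positive rate to about 20%, and because the design can largely avoid it. The rating is that it should be fixed: a cheap improvement, not a defect that invalidates the study.

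**What to change.** In the Measurements section, keep three samples but take awakening, +30 minutes and bedtime in that order on one calendar day, starting no earlier than the day after the questionnaires are completed. State the same rule on the sheet sent with posted follow-up kits. The diary covariates then describe the day on which all three samples were taken, and the wording in Statistical analysis and Discussion can stand.

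**Cost:** a reworded instruction sheet and diary, with no extra samples, assays or visits. The kit is held about a day longer and some bedtime samples may be missed, so completeness should be monitored.

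**If the present order must stay:** restate the primary outcome in Statistical analysis and Discussion as an evening-to-next-morning contrast, describe the mean in the same way, and say which calendar day the diary covariates refer to. Record the interval from questionnaire to bedtime sample and use it in a sensitivity analysis of the group comparison.

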In addition, the mechanisms through which DVA causes mental and physical conditions are very poorly studied. One mechanism that may contribute to stress-related disorders is the hypothalamic-pituitary-adrenocortical (HPA) axis, which produces cortisol [11-13]. Cortisol activity in healthy children and adults follows a consistent diurnal pattern with peak levels of output observed within the first 30–40 min after awakening followed by a progressive reduction throughout the morning and afternoon with a nadir around midnight [14]. Cortisol levels naturally increase in response to exposure to acute stress and helps organisms cope with a short term homeostatic challenges by modification of metabolic and cognitive function [15]. Chronic stress has the capacity to increase or decrease HPA activity, and the resulting pattern depends, both on features of the stressor and the person facing it. Female survivors describe DVA as traumatic uncontrollable stress that poses a threat to their physical and social self, and is associated with feelings of shame [16]. There are very few studies focused on assessing physiologic correlates of chronic stress in abused women.

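### The awakening sample waits for waking and readiness to get up, while the cortisol awakening response is defined from awakening; any gap between the two can bias it

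*Protocol article*

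**What the plan says.** The protocol article asks for three saliva samples at each assessment (Measurements). After the bedtime sample, the awakening sample is due "next morning as soon as the woman wakes up and is ready to get up for the day". The post-awakening sample is due "30 minutes after taking awakening sample", so its clock starts at the second sample and not at waking.

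The Statistical analysis section names as a secondary outcome "CAR, size of post-awakening surge in cortisol that occurs in 30 minutes after awakening". Here the clock starts at awakening. The Background describes the normal diurnal pattern as having "peak levels of output observed within the first 30–40 min after awakening".

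Three other statements under Measurements bear on the point. The instruction sheet gives hints such as "putting the tube next to the bed for morning sample". The diary collects, among other covariates, "schedule (whether weekend vs. weekday), time of awakening, lifestyle". An abstention rule also applies: "Participants must have waited at least 30 minutes after smoking, consuming any food or drink or teeth brushing" before a sample is taken.

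**The concern.** The instruction for the awakening sample sets two conditions, waking and readiness to get up. If they do not coincide, the later one governs. A woman who lies awake for some minutes then gives a first sample that is already on the morning rise. Because the third sample is timed from it, that sample falls at 30 minutes plus the gap. With a long enough gap it comes after the peak, and the measured difference is no longer the quantity defined in the Statistical analysis section.

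CAR is a named secondary outcome and one of the key parameters in objective 1. It is also among the cortisol outcomes considered as mediators in objective 3. Recorded times could show afterwards that a first sample was late, but they cannot recover the missed waking value. The wording therefore needs settling before collection.

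**Working it through.** **The plan's own figures.** The article gives no figure for sampling delay or for error in CAR, so there is none to reproduce on this point. The sample-size figures are not affected. A two-sample t-test for 0.5 SD, 80% power and 0.05 (two-sided assumed) gives 63.8, so 64 per group and 128 in all; 128/0.6 = 213.3 and 213/0.6 = 355, as stated.

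**Inputs from the article.** The CAR window is 0 to 30 minutes after awakening (Statistical analysis). The peak time T is 30–40 minutes after awakening (Background). The third sample is 30 minutes after the second (Measurements).

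**Assumptions.** The gap d between waking and the second sample is not documented, so 5 to 20 minutes is tried. The shape of the curve is also assumed.

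**Step 1: when the third sample passes the peak.** It is taken at 30 + d minutes after waking. This exceeds T when d > T − 30, which means any gap if T = 30, over 5 minutes if T = 35, and over 10 minutes if T = 40. A gap over 10 minutes is therefore past the peak for every peak time in the Background. At 10 minutes or less the sample still lies at 30–40 minutes.

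**Step 2: linear rise.** Let cortisol rise by 1 unit per minute to T, then fall by k units per minute, with k = 0, 0.25 or 0.5.

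- Defined CAR: C(30) − C(0) = 30.
- Measured CAR: C(30 + d) − C(d).
- If d ≤ T − 30, this is (30 + d) − d = 30, so nothing is lost.
- If d > T − 30, it is T − k(30 + d − T) − d, and the share lost is (1 + k)(30 + d − T)/30.

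Example with d = 15 and T = 35: 10/30 = 33% for k = 0, and 1.5 × 10/30 = 50% for k = 0.5.

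| Gap d | T = 30 | T = 35 | T = 40 |
|---|---|---|---|
| 5 min | 17–25% | 0% | 0% |
| 10 min | 33–50% | 17–25% | 0% |
| 15 min | 50–75% | 33–50% | 17–25% |
| 20 min | 67–100% | 50–75% | 33–50% |

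At a 15-minute gap the first morning sample already holds 15/40 = 38% to 15/30 = 50% of the rise.

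**Step 3: other shapes.** With a linear, concave or sigmoid rise, T = 30, 35 or 40, and a linear fall back to the waking level over 45 or 90 minutes, the ratio of measured to defined CAR is:

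| Gap d | Ratio, lowest to highest |
|---|---|
| 0 min | 1.00 |
| 5 min | 0.63 to 1.08 |
| 10 min | 0.28 to 1.00 |
| 15 min | −0.04 to 0.76 |
| 20 min | −0.31 to 0.52 |

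At 5 minutes the error can be downward, nil or slightly upward (at most +8%, with a sigmoid rise and a 40-minute peak). At 10 minutes it is downward or nil. At 15 and 20 minutes every curve tried gives a value that is too low.

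**Step 4: would timing the third sample from waking help?** If the second sample is late by d and the third is taken 30 minutes after waking, the linear rise gives 30 − d, a loss of d/30: 33% at 10 minutes and 50% at 15. As written, with T = 35, the losses are 17–25% and 33–50%. Re-anchoring only the third sample is therefore no better with that peak. It helps when the peak is near 30 minutes and the curve then falls.

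**The case against.** The strongest reply is that the article also contains wording that limits any delay. The instruction itself calls for prompt sampling on waking, the sample is named for awakening, and the tube is to be kept by the bed. With no delay the samples fall at 0 and 30 minutes, exactly as CAR is defined. The phrase about getting up may also serve a purpose, to separate the final awakening from waking in the night. The article condenses an illustrated sheet that is not shown, and the Discussion says that participant documents were amended after a pilot and advisory-group guidance.

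Much of this stands. A reader might infer that CAR is measured late and biased low in this study. The article does not support that as a fact, because it gives no delay and because short delays can leave CAR unbiased or slightly high.

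A reader might also infer that the primary outcome is affected. The Statistical analysis section describes only a decline in cortisol across the day and does not say which morning sample anchors it.

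Nor does the article support a biased comparison between abused women and controls, or between women with and without depression or PTSD. It has no data on time awake before rising in any group. The abstention rule could lengthen the gap for a woman who smokes, eats, drinks or brushes her teeth first, but how often that happens is unknown. The listed diary items do not include sample clock times, but a condensed article may leave these to the full protocol, so this is not counted as an omission.

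The reply does not remove the second condition from the instruction or the difference in anchors between the two sections.

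**Conclusion.** The concern holds as an inconsistency that can bias a secondary outcome. Measurements and Statistical analysis describe the same CAR only if the awakening sample is taken at waking, and the instruction as worded allows it to be later.

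For gaps over about 10 minutes, CAR is too low for every peak time in the Background under the curves assumed. At 15 minutes the loss is about 17–75% with a linear rise, and 24% to just over 100% across the second set of curves. For shorter gaps the error depends on the curve and may be nil. These figures show how sensitive CAR is to delay. They do not estimate the error in this study, because the gap and the shape of the curve are both assumed; a rise that accelerated all the way to a late peak could even reverse the direction.

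The point is worth correcting before collection because a missed waking value cannot be recovered. It does not undermine the sample size, and no effect on the primary outcome has been shown.

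**What to change.** Reconcile the two sections by fixing the second sample at waking:

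- Word the awakening sample as: immediately on your final awakening, while still in bed, before getting up. This keeps any intended distinction from waking in the night.
- Keep the third sample 30 minutes after the second. With the second sample at waking, both then match the CAR definition. Do not re-time only the third sample from waking, for the reason in step 4 of the working.
- Record the waking time and both morning sample times, if the full diary does not already do so.
- Add a sensitivity analysis that excludes CAR values whose first sample was late by more than a number of minutes set in advance.

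The cost is a small wording change to the instruction sheet and diary, with no extra samples, and the loss of some CAR values in the sensitivity analysis.
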